#### Secondary objectives

Secondary objectives of this trial are to measure the effect of IV lidocaine, compared to placebo, on:Pain intensities (NRS 0-10) at rest and movement on postoperative days (PODs) 1–3;Oral morphine-equivalent opioid consumption on POD 1–3, 3 months, and 1 year after surgery;Persistent pain at 1 year after surgery;Moderate-to-severe persistent pain (NRS ≥ 4 at rest) at 3 months and 1 year after surgery;Persistent neuropathic pain (defined by Douleur Neuropathique 4 [DN4] symptoms assessment) at 3 and 12 months after surgery;Sensory and affective qualities of pain (Short Form McGill Pain Questionnaire 2) at 3 months and 1 year after surgery;Emotional functioning (Profile of Mood States [POMS]) at 3 months and 1 year after surgery;Physical functioning (Brief Pain Inventory [BPI]) at 3 months and 1 year after surgery;Quality of life (EQ-5D-5L) at 3 months and 1 year after surgery;Cancer recurrence at 12 months;Adverse events; adverse drug related events within 24 h of infusion and serious adverse events throughout the trial conduct;Cost-effectiveness.

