Additionally, all patients will be asked about their emotional and physical functioning, and their quality of life at the 3- and 12-month follow-up. Emotional functioning will be evaluated using the POMS, which is a reliable instrument, validated in a breast cancer population to evaluate aspects of psychological distress (e.g., depression, anxiety, anger) [57]. Physical functioning will be measured by the interference scale of the BPI, which provides a reliable and valid assessment of interference of pain on level of functioning and has been used in a variety of post-mastectomy pain trials [58–60] and in patients with breast cancer pain [61–64]. Given the well-established inverse relationship between pain and quality of life [65, 66], we will use the EQ-5D-5L [67], which is a widely used measurement tool for assessing health-related quality of life [68]. This instrument is also commonly used in health economic evaluations, which will be explored if lidocaine infusions are shown to be significant for the primary outcome.

Cancer recurrence will be assessed at 3 and 12 months. If cancer recurrence is suspected during follow-up, RAs will review with their respective Site Principal Investigator (PI) and send relevant source documents to the coordinating center. If needed, this outcome will be sent for adjudication by two independent investigators blinded to the patient’s treatment allocation.

Adverse events (AE) will be monitored as a secondary safety outcome. Adverse events will be defined as “any noxious and unintended response to an Investigation Medicinal Product (IMP) related to any dose.” Given the half-life of lidocaine is approximately 90 min, screening for adverse events will be limited to the period of administration (intraoperative period), and immediate postoperative period (up to 24 h after surgery). AEs will be screened and reported by the attending anesthesiologists administering study medications intraoperatively and by RAs reviewing postoperative medical records. Serious adverse events (SAEs) will be monitored throughout the entire trial conduct.

Cost-effectiveness will be assessed if lidocaine significantly reduces persistent pain at 3 months to determine cost-savings from a patient and societal perspective if lidocaine is adopted widely into practice.

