Study patients will be followed up in the post-anesthesia care unit (PACU) within 1 h of surgery, on PODs 1 to 3, and at 3 and 12 months after surgery. Sites can follow-up with patients electronically via approved online platforms (e.g., MS Teams, Zoom), traditional data collection methods (i.e., telephone follow-up), or both. REDCap allows electronic follow-up surveys which can be used to collect self-reported data. A secure patient-specific link is sent via email or text message to collect self-reported data on PODs 1, 2, and 3 (pain scores, opioid consumption, and adverse events). Patients that follow-up via traditional methods will be trained to complete a paper pain diary before hospital discharge to record their acute pain (pain at rest and movement) scores, opioid consumption, and any adverse events. RAs will call patients on POD 1 to remind them to complete their pain diary and again on POD 4 to obtain data from their pain diary over the phone—this method was used in the pilot and achieved > 98% data collection [36]. For data corroboration, we will ask patients to bring their paper pain diary to their next visit with their surgeon or to submit it electronically. The 3- and 12-month follow-up visit will occur electronically or via a telephone interview [70]. To ensure retention at the 3- and 12-month follow-ups, we obtain contact information from patients, including their relatives and care givers. If we do not hear from a patient at the 3- or 12-month follow-up, we will mail the questionnaires to their home with a pre-paid envelope to complete and return to the site recruitment center.

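### Adverse events are defined as reactions to the study drug within 24 h of surgery, while patients report any adverse event over PODs 1–3

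*Protocol article*

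**What the plan says.** Four parts of the protocol article bear on adverse events.

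- **Secondary outcomes, definition.** An adverse event is "any noxious and unintended response to an Investigation Medicinal Product (IMP) related to any dose".
- **Secondary outcomes, window and source.** Citing a lidocaine half-life of about 90 min, the article says "screening for adverse events will be limited to the period of administration (intraoperative period), and immediate postoperative period", the latter running to 24 h after surgery. On source: "AEs will be screened and reported by the attending anesthesiologists administering study medications intraoperatively and by RAs reviewing postoperative medical records". Serious adverse events are followed for the whole trial.
- **Secondary objectives.** The safety objective covers "adverse drug related events within 24 h of infusion and serious adverse events throughout the trial conduct".
- **Recruitment and participant timeline.** Electronic links are used to "collect self-reported data on PODs 1, 2, and 3 (pain scores, opioid consumption, and adverse events". Patients followed by traditional methods keep a paper diary to "record their acute pain (pain at rest and movement) scores, opioid consumption, and any adverse events". Research assistants collect the diary data by telephone on POD 4.

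The Analysis section then plans counts and proportions of adverse events by arm, with an exploratory comparison between groups. It attaches no attribution condition.

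**The concern.** There are two problems, and both lie in stated text.

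First, the definition makes relation to the drug a condition for being an adverse event at all. In a randomized, blinded, placebo-controlled trial, the difference between arms already shows what the drug adds. Nobody needs to decide case by case whether lidocaine, the anesthetic or the operation caused an episode. A clinician who follows the definition literally must form that opinion without knowing the allocation, and may never record events thought unrelated. A later analysis plan cannot recover events that were not recorded.

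Second, the defined outcome and the collected data do not match. The definition covers 24 h, clinician and chart sources, and drug reactions. The follow-up procedures cover PODs 1–3, patient self-report, and any event.

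The stakes are moderate. The Background names safety among the important secondary outcomes that earlier small trials could not explore, and the abstract foresees lidocaine becoming standard of care if the trial succeeds. The table of non-serious events is therefore likely to be read closely.

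**Working it through.** The plan gives no figure for adverse events, so there is none to reproduce. The check is mainly a comparison of text.

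| Feature | Secondary objectives | Secondary outcomes | Recruitment and participant timeline | Analysis |
|---|---|---|---|---|
| What counts | Drug-related events; serious events | Response to the study drug; serious events | Adverse events (link); any adverse event (diary) | Adverse events, unqualified |
| Window, non-serious | 24 h | Surgery plus 24 h | PODs 1, 2 and 3 | Not stated |
| Anchor | Infusion | Surgery | Postoperative day | Not stated |
| Source | Not stated | Anesthesiologist; chart review | Patient self-report | Not stated |

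**Definition.** The objectives and the outcomes section agree that non-serious events must be drug-related. The diary carries no such condition, and patients cannot be expected to apply one.

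**Window.** Collection to the end of POD 3 runs about two days past the 24 h limit. Self-reports from PODs 2–3 are collected but fall outside the defined outcome.

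**Anchor.** The infusion may continue for up to 30 min in the recovery room. If 24 h is counted from the end of infusion, it closes up to 30 min later than 24 h from the end of surgery. If it is counted from the start, it closes earlier by roughly the length of the operation. The discrepancy is small but needs one answer.

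**Source.** The outcomes section names clinicians and charts only. Whether a self-report counts is therefore unclear even within the first 24 h.

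**Can the effect of attribution be sized?** Only under assumptions. Take 1602 / 2 = 801 per arm and assume true all-cause risks of 6% with lidocaine and 3% with placebo. Neither rate is in the documents. The formulas are

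SE = √[(p₁(1 − p₁) + p₂(1 − p₂)) / 801], power ≈ Φ(|p₁ − p₂| / SE − 1.96).

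- No filter: SE = √[(0.06 × 0.94 + 0.03 × 0.97) / 801] = 0.0103; 0.03 / 0.0103 ≈ 2.91; power ≈ 0.83.
- Half of all events discarded (3% vs 1.5%): SE = √[(0.03 × 0.97 + 0.015 × 0.985) / 801] = 0.0074; 0.015 / 0.0074 ≈ 2.03; power ≈ 0.53.

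Now discard half of the background (3% becomes 1.5%) but vary the share of the true excess of 3 percentage points that is kept:

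| Excess kept | Risks compared | Power |
|---|---|---|
| 50% | 3.0% vs 1.5% | 0.53 |
| 70% | 3.6% vs 1.5% | 0.76 |
| 78% | 3.84% vs 1.5% | 0.83 |
| 90% | 4.2% vs 1.5% | 0.90 |
| 100% | 4.5% vs 1.5% | 0.94 |

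Under these rates, attribution lowers the chance of seeing a difference if less than about 78% of true drug effects are kept, and raises it if more are kept. The documents do not say which case applies.

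**The case against.** The strongest reply is that this is a wording mismatch with little reach. Several parts of that reply stand.

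- **A reader might infer that the safety result will be too reassuring**, for example that power falls from 0.83 to 0.53. The documents do not support this. The rates are assumed, the effect reverses if clinicians retain most true drug effects, and those who report events are blinded to allocation. Power is also a weak yardstick for a comparison that the plan calls exploratory.
- **A reader might infer that the Secondary objectives contradict the definition**, listing adverse events and drug-related events as two separate outcomes. The item reads more naturally as a heading followed by two components: drug-related events to 24 h, and serious events throughout. That agrees with the Secondary outcomes section.
- **A reader might infer a formal causality step.** The article describes none. The filter follows from the definition if it is applied literally; whether sites apply it that way is not known.
- **Serious events are covered.** They are followed throughout, and the data safety and monitoring board reviews both expected and unexpected ones. Its remit also includes the definitions of adverse events.
- **Tabulation detail may sit elsewhere.** The analysis plan is not finished, and a separate operational protocol exists. The absence of tabulation rules from the article is therefore not the point.

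The objection does not remove the stated definition or the stated 24 h limit, which conflict with the stated POD 1–3 collection. The half-life gives a reason for a short window, but none for requiring attribution or for collecting beyond the window without saying what those reports are for.

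**Conclusion.** The point holds for non-serious adverse events. As written, they count only if thought to be a reaction to the study drug. The 24 h window does not match the POD 1–3 self-reports, and its anchor and source differ between sections.

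The conclusion rests on the article's own text and on one assumption: that sites apply the definition as written. No numerical size can be given. Under the assumed 6% vs 3%, with half of background events dropped, power ranges from 0.53 to 0.94 as the retained share of the true excess goes from 50% to 100%, against 0.83 with no filter. Neither a direction nor a magnitude of distortion is established. The primary result and the monitoring of serious adverse events are unaffected.

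**What to change.** - **Definition.** Define an adverse event as any untoward medical occurrence after study drug starts, whatever its relation to the drug. Record relatedness in a separate field, completed blind to allocation.
- **Analysis.** Tabulate by arm all recorded events regardless of attribution. Show drug-related events as a secondary display.
- **Window, anchor and source.** Reconcile the Secondary objectives, Secondary outcomes, Recruitment and participant timeline, and Analysis sections. State one anchor for the 24 h. Tabulate the 24 h clinician and chart data separately from the POD 1–3 self-reports, which are already being collected.

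The cost is protocol and case report form wording, plus more expected postoperative events to record and tabulate. There is one limit that wording cannot remove. Recruitment began in September 2021 and was expected to finish in mid-2025, so many patients were enrolled under the current definition. If sites applied it literally, all-cause data for those patients may be incomplete and not fully recoverable. The report should say so and identify the date from which the new definition applied.

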### Recruitment and participant timeline

We will use recruitment strategies that we developed in our pilot trial and prior perioperative studies [36, 69]. We aim to approach patients through involved breast surgeon offices, as well as screening daily preoperative assessment clinic lists, operating room booking lists, incoming patient lists on surgical wards, and monitor operating room procedure lists for add-on surgeries. Study RAs will approach eligible patients to verify eligibility, either in person or remotely, and to obtain voluntary informed consent. In some cases, where it may not be possible for the prospective participant to sign the informed consent form, verbal consent will be obtained and baseline questionnaires will be provided to the patient. The expectation remains that the consent form will be signed and documented in-person prior to surgery. Patients may also sign the consent form online via REDCap and no study interventions will occur prior to written consent. Further, patients have the right to withdraw from the study at any time for any reason, without the need to justify their decision.

RAs will randomize patients through an online 24-h, interactive, web-based randomization system. Randomization will occur on the day of surgery to minimize the risk of surgery being postponed or cancelled after randomization. For logistical reasons, sites have the ability to randomize the day before to allow ample time for study drug preparation, or on a Friday for a Monday case.

Study patients will be followed up in the post-anesthesia care unit (PACU) within 1 h of surgery, on PODs 1 to 3, and at 3 and 12 months after surgery. Sites can follow-up with patients electronically via approved online platforms (e.g., MS Teams, Zoom), traditional data collection methods (i.e., telephone follow-up), or both. REDCap allows electronic follow-up surveys which can be used to collect self-reported data. A secure patient-specific link is sent via email or text message to collect self-reported data on PODs 1, 2, and 3 (pain scores, opioid consumption, and adverse events). Patients that follow-up via traditional methods will be trained to complete a paper pain diary before hospital discharge to record their acute pain (pain at rest and movement) scores, opioid consumption, and any adverse events. RAs will call patients on POD 1 to remind them to complete their pain diary and again on POD 4 to obtain data from their pain diary over the phone—this method was used in the pilot and achieved > 98% data collection [36]. For data corroboration, we will ask patients to bring their paper pain diary to their next visit with their surgeon or to submit it electronically. The 3- and 12-month follow-up visit will occur electronically or via a telephone interview [70]. To ensure retention at the 3- and 12-month follow-ups, we obtain contact information from patients, including their relatives and care givers. If we do not hear from a patient at the 3- or 12-month follow-up, we will mail the questionnaires to their home with a pre-paid envelope to complete and return to the site recruitment center.

### Unblinding

In cases of suspected lidocaine toxicity, patients will be treated according to standard clinical algorithms for the management of lidocaine toxicity as described by the American Society of Regional Anesthesia [71, 72]. This algorithm includes the administration of intralipid, the antidote for lidocaine toxicity. Intralipid is a lipid emulsion with a high safety profile available at all involved clinical sites in this trial. Intralipid has no known adverse reactions in those without lidocaine overdose, and as such, intralipid will be administered only on suspicion of lidocaine toxicity without unblinding patient’s group allocation. If circumstances arise requiring unblinding of patient’s group allocation, local site investigators will contact the Coordinating Centre to discuss unblinding decisions jointly. All efforts will be made to avoid unnecessary unblinding and the decision to unblind will be made on a case-by-case basis.

### Sample size

Only a few prospective studies provide data on the prevalence of persistent pain at 3 months after breast cancer surgery, with estimates ranging from 33 to 82% [32, 34, 49, 73, 74]. The largest study (*n* = 150) reported a 33% prevalence at 3 months; however, only 84 (56%) patients provided follow-up data. Our pilot (*n* = 100), conducted at two Canadian centers, found a prevalence of persistent pain of 58.3% (95% CI 38.6 to 78.1%) in the control group at 3 months. Furthermore, our pilot found a 32% relative risk reduction (RRR) with the use of IV lidocaine, whereas Grigoras et al. [32] and Kim et al. [34] found a 75 and a 50% RRR at 3 months, respectively. We believe these RRR estimates are likely overestimations of the true treatment effect given the small size of the trials, the multiple pathogenic mechanisms involved, and the rarity of such large effect sizes in the medical literature [75, 76] and within chronic pain prevention trials [77].

We have therefore chosen to design our trial to identify a plausible, but clinically important, 25% RRR while using 30% as the control group pain prevalence at 3 months. To achieve 90% power to detect in a two-sided comparison with *α* = 0.05, and 10% loss-to follow-up, we will need a sample of 1602 participants. For a fixed RRR, power increases as the control group prevalence increases. This sample size also provides adequate power to inform realistic RRRs in important but less common secondary outcomes such as presence of moderate-to-severe pain. For example, based on a control group prevalence of moderate-to-severe pain of 16% in our pilot, we have 80% power to detect a RRR of 31% or greater.

### Analysis

A statistical analysis plan (SAP) has not yet been completed and approved by the Steering Committee. In general, the analysis of results will be completed in the following manner but is subject to minor changes in the SAP. Patients will be analyzed according to their allocated treatment group (intention-to-treat analysis). No imputations will be made for missing data. The relative risk for the primary outcome of the presence of persistent pain at 3 months will be estimated (along with its 95% CI) from a log-binomial model that includes factors for treatment group and the stratification variables (study center, breast reconstruction). If the number of centers is large, a center will be represented by a random effect [78]. A similar analytical approach will be used for secondary binary outcomes. Treatment effects will also be quantified by calculating absolute differences between intervention groups. Analyses of continuous variables such as acute pain NRS scores at rest and movement, oral morphine-equivalent opioid consumption, time to hospital discharge, scores on SF-MPQ-2, POMS, BPI, and EQ-5D-5L will use linear regression (with transformations of outcomes if necessary) to estimate treatment effects and their 95% CIs, again with factors (or random effects) for stratification variables. Baseline characteristics in each group will be summarized without any comparative analyses. If more than 5% of participants are missing the primary outcome, the primary analysis will combine results across multiple imputed datasets, generated from a regression model using other available pain measurements. Analysis of adverse events will be summarized using count and proportions in each intervention group (lidocaine and placebo groups) and numerical values will be used for exploratory analysis between groups. All statistical analyses will be performed using the R statistical language.

Analysis of trial outcomes will be completed at the end of the trial. There will be no interim analysis for efficacy due to the possibility of introducing bias and over-estimating treatment effects [79–81].

We plan to conduct three a priori subgroup analyses to determine whether there is a differential effect of an intraoperative lidocaine infusion on (1) those who underwent a mastectomy versus a lumpectomy; (2) those who underwent an axillary lymph node dissection versus a sentinel lymph node biopsy/no lymph node removal; (3) those who received radiotherapy versus those who did not. The corresponding analyses will use the log-binomial model and include an interaction between the subgroup and treatment variables. We hypothesize that patients with mastectomies and axillary lymph node dissections will benefit more than their respective comparators given that these procedures are associated with greater surgical-induced nerve injury and, thus, may be more responsive to the effect of lidocaine [10]. We also expect that patients not receiving radiotherapy would demonstrate a greater effect of lidocaine since those who receive radiotherapy receive their treatment postoperatively, exposing them to a source of nerve injury that cannot be mitigated through the use of lidocaine during surgical resection.

We will conduct a within-trial cost-effectiveness analysis, using societal and patient perspectives and the trial time horizon (12 months). For general health-related quality of life, we will use the EQ-5D-5L [82, 83] and for healthcare costs we will use a structured healthcare use survey. Unit costs for healthcare services will be obtained from the respective Canadian sources [84, 85]. We will follow the Canadian economic evaluation guideline [86]. The cost-effectiveness will be estimated by the incremental cost-effectiveness ratio (ICER) measuring the cost per additional quality-adjusted life year (QALY) when comparing the lidocaine arms to placebo. We will also conduct incremental net-benefit (INB) analysis using accepted willingness-to-pay thresholds. Uncertainty in cost-effectiveness analysis will be evaluated by bootstrapping and by cost-effectiveness acceptability curves [87]. Analysis will be conducted only if lidocaine is found to significantly reduce persistent pain at 3 months (primary outcome).

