## Background

### Persistent pain after breast cancer surgery

Breast cancer is the most commonly diagnosed cancer globally (2.3 million cases annually; ~ 12% of cancer diagnoses) [1] and the second most common type of cancer diagnosed in Canada (28,000 cases annually), despite it almost exclusively affecting females [2]. Fortunately, advances in cancer screening and management have substantially improved its prognosis, leading to a 85-90% 5-year survival rate in developed countries [1]. Increased survivorship has led, however, to the identification of important and problematic long-term complications from breast cancer management, specifically the devastating effects of persistent pain.

Breast cancer surgery is a critical component to breast cancer treatment. A common, yet vastly under-recognized complication after breast cancer surgery, including mastectomy and segmental mastectomy (lumpectomy), is persistent pain, often referred to as post-mastectomy pain syndrome (PMPS). PMPS is pain around the surgical incision (axilla, medial arm, shoulder, or chest wall on the side of surgery) that does not resolve, or worsens, ≥ 3 months after surgery (time needed to heal from a surgical incision) [3–5]. Unfortunately, breast cancer surgery has one of the highest rates of persistent pain among all surgical sub-types [6, 7]. In a recent systematic review of patients undergoing breast cancer surgery (146 studies, *n* = 137,675), the prevalence of persistent pain after breast cancer surgery was 35% (95% confidence interval [CI] 32 to 39%) [8]. Further, 20% of patients with persistent postsurgical pain report that their pain is moderate to severe in intensity (numeric rating scale [NRS] ≥ 4) [8–10]. Persistent pain after breast cancer surgery is chronic—over 50% of those afflicted will continue to suffer from it 7–12 years after surgery [11]. These are staggering statistics given that > 22,000 Canadians undergo breast cancer surgery each year [2] and younger patients (< 40 years) are at greater risk of this complication [12]. Persistent pain has a tremendous impact on quality of life as it causes emotional distress, mood disturbance, impaired sleep, and reduced physical functioning [13–16]. These deleterious effects of PMPS are experienced at a societal level through direct (healthcare costs) and indirect (loss of productivity) expenses, totaling $1 billion USD a year in the USA alone [17].

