### Randomization

A statistician not involved in the study analysis will generate an online encrypted randomization list. Randomization will use permuted blocks of varying size and will be stratified by center and breast reconstruction (i.e., immediate reconstruction surgery with implants at the time of index surgery). Patients will be randomized in a 1:1 ratio between lidocaine and placebo. Research assistants (RAs) will randomize patients through an online 24-h, interactive, web-based randomization system. Randomization will occur on the day of surgery to minimize the risk of surgery being postponed or cancelled after randomization. For cases performed first thing in the morning, if needed patients could be randomized the night before.

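### The primary model adjusts only for center and reconstruction; prespecifying age and planned procedure would add a small, low-cost gain in precision to an analysis that is already valid

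*Protocol article*

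**What the plan says.** The Analysis section of the protocol article obtains the primary relative risk and its 95% CI "from a log-binomial model that includes factors for treatment group and the stratification variables (study center, breast reconstruction"), with center as a random effect if there are many centers. It adds: "Treatment effects will also be quantified by calculating absolute differences between intervention groups". The section describes itself as a general outline, open to minor changes in an analysis plan that was not yet complete.

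The covariates match the design. According to the Randomization section, allocation "will be stratified by center and breast reconstruction (i.e., immediate reconstruction surgery with implants at the time of index surgery").

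Elsewhere the article touches on two other baseline characteristics:

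- **Age.** The Background subsection on persistent pain states that patients under 40 "are at greater risk of this complication".
- **Procedure.** The subgroup paragraph under Analysis says of mastectomy and axillary dissection that "these procedures are associated with greater surgical-induced nerve injury". The Background says nerve injury during resection may be the inciting event of the syndrome.

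The inclusion criteria admit everything from unilateral lumpectomy to bilateral mastectomy, so these characteristics vary across the sample. The abstract enrols adults scheduled for one of the two operations, so the planned operation, like age, is known before randomization.

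**The concern.** If age and procedure predict pain at 3 months, the variation in risk that they explain stays in the residual of the primary comparison. The confidence interval is then somewhat wider than the available data require, and a chance imbalance in either variable is not corrected in the estimate. What is at stake is efficiency on the main result; validity is not affected. The question is whether the gain is large enough to be worth prespecifying.

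**Working it through.** **1. The plan's own figure.** The Sample size section uses a "25% RRR while using 30% as the control group pain prevalence at 3 months", so 30% against 22.5%, and states: "To achieve 90% power to detect in a two-sided comparison with *α* = 0.05, and 10% loss-to follow-up, we will need a sample of 1602 participants". With average risk (0.30 + 0.225)/2 = 0.2625, the pooled formula gives, per arm,

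n = [1.96·√(2·0.2625·0.7375) + 1.2816·√(0.30·0.70 + 0.225·0.775)]² / 0.075² = (1.2196 + 0.7945)² / 0.005625 ≈ 721.

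Then 2·721/0.9 = 1602. Rounding up to 722 per arm gives 1605; unpooled and arcsine versions give 1598 and 1600. Power with 1602·0.9 ≈ 1442 evaluable patients and no covariates is 90.0%. The claim stands and does not depend on any covariate gain.

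**2. Assumptions.** The documents give no effect size for age or procedure. Assumed here: age SD 12 years, odds ratio 0.85 (weak) to 0.75 (strong) per decade; 40% mastectomy, odds ratio 1.1 (weak) to 1.3 (strong).

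**3. Explained variance.** R² = Var(p)/[p̄(1 − p̄)], where p is the patient's risk under a logistic model with mean p̄ = 0.2625. As a hand check, R² ≈ p̄(1 − p̄)·Var(linear predictor):

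- Weak: (1.2·ln 0.85)² + 0.24·(ln 1.1)² = 0.0380 + 0.0022 = 0.0402; times 0.1936 = 0.0078. Exact value: 0.0077.
- Strong: (1.2·ln 0.75)² + 0.24·(ln 1.3)² = 0.1192 + 0.0165 = 0.1357; times 0.1936 = 0.0263. Exact value: 0.0254.

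**4. Power and equivalent patients.** Power = Φ(3.2415/√(1 − R²) − 1.96); equivalent extra patients = 1602/(1 − R²) − 1602.

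| | R² | SE reduction | Power | Extra patients |
|---|---|---|---|---|
| Now | 0 | 0 | 90.0% | 0 |
| Weak | 0.8% | 0.4% | 90.2% | 12 |
| Strong | 2.5% | 1.3% | 90.7% | 42 |

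**5. A second set of assumptions.** Treat age as under 40 or not (5-10% of patients, risk ratio 1.3-2.0) and mastectomy as 40-50% of patients with risk ratio 1.2-2.0. R² is then 0.4% to 7.3% and power 90.1% to 92.0%; the upper end needs both risk ratios to be 2. Simulation of 2000 trials of 1442 patients per scenario (Poisson regression with robust SE) gave:

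| Under 40: share, RR | Mastectomy: share, RR | Mean SE of log RR, without → with covariates | Power |
|---|---|---|---|
| 10%, 1.5 | 40%, 1.2 | 0.0898 → 0.0894 | 90.3% → 90.3% |
| 10%, 1.5 | 40%, 1.5 | 0.0897 → 0.0887 | 90.1% → 90.6% |
| 10%, 2.0 | 50%, 2.0 | 0.0898 → 0.0868 | 90.4% → 92.5% |

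**6. Chance imbalance.** With 721 per arm and 40% mastectomy, the SD of the between-arm difference in mastectomy share is √(0.4·0.6·2/721) = 2.6 points. For a mastectomy risk ratio of 1.5 at 30% overall risk, the two risks are 25% and 37.5%. A two-SD imbalance (5.2 points) moves the risk difference by 0.052·12.5 ≈ 0.65 points, against a target of 7.5.

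**The case against.** The strongest reply is that nothing here is wrong. Adjusting for the stratification factors is an accepted primary analysis, the power claim is met without further covariates, and extra baseline covariates are a normal matter for the pending analysis plan. The confidence interval already allows for chance imbalance. All of this stands, and it limits the point to an efficiency suggestion. It does not remove the point, because the article lists the model terms and there is still time to extend them.

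The gain may also be smaller than computed. The calculation starts from a model with no covariates, whereas reconstruction is already included and plausibly overlaps with mastectomy and age. This stands too.

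Nor is adjustment entirely free. A log-binomial model can fail to converge, and continuous age with many center terms makes that more likely.

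Four stronger readings are tempting, but the documents do not support them:

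- **A gain of more than 100 patients.** Combined with strong age and mastectomy effects, axillary dissection (assumed odds ratio up to 2.4) and a baseline score (up to 1.4 per SD) would bring R² to about 7.3%, or roughly 126 patients. No passage says that planned axillary surgery or such a score is recorded before randomization. The subgroup paragraph refers to surgery undergone. The consent procedure mentions baseline questionnaires without their content, and the article schedules the mood, function and quality-of-life scales at 3 and 12 months.
- **Procedure plainly named as a cause of pain.** The subgroup paragraph links it to nerve injury in order to predict a larger lidocaine effect. That it also predicts pain is an inference through the Background's tentative account of mechanism.
- **An unadjusted absolute difference.** The text does not say whether that difference is adjusted.
- **A biased or underpowered primary result.** Neither follows.

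**Conclusion.** The point holds as a small, low-cost improvement. The article names younger age as a risk factor and gives reason to think procedure is prognostic, yet the primary model uses neither. On the assumed odds ratios for these two variables, adjustment would raise power from 90.0% to about 90.2-90.7%, equal to about 12 to 42 patients of 1602. Under the weaker risk-ratio assumptions the gain is negligible, and it would approach two power points or slightly more only if both variables roughly doubled the risk. All of these sizes rest on assumed prognostic strengths and prevalences. The planned analysis remains valid as written.

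**What to change.** In the analysis plan, before unblinding:

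- Add age (continuous) and planned procedure (lumpectomy or mastectomy, unilateral or bilateral) as prespecified covariates of the primary model, alongside center and reconstruction.
- Add planned axillary surgery or a baseline score only if it is recorded before randomization. Do not add radiotherapy, which is given after surgery.
- Name a fallback in case the log-binomial model does not converge: Poisson regression with robust standard errors, or a relative risk and risk difference standardized from a logistic model.
- Keep the model with stratification variables only as a sensitivity analysis.

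The cost is some wording and a few lines of code, with no new patients. Age and the scheduled operation are already known. The small downsides are the need for a rule for the few missing baseline values and for the convergence fallback.
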